Endovascular treatments are associated with greater cost than OSR due to the cumulative costs of the stent-grafts, ancillary devices, postoperative surveillance and re-intervention. National Health Service (NHS) clinical service commissioners have noted an increasing demand for FEVAR in the absence of evidence regarding clinical effectiveness identifying which patients would benefit from this procedure and whether the substantial cost associated with the technique is an appropriate use of NHS resources. Prohibitive cost and lack of experience with FEVAR in many arterial centres have concomitantly led to a substantial use of off-label standard EVAR in complex neck anatomy, an intervention that is known to have poorer long-term results compared with on-label EVAR.^17^ The National Institute for Health Research Health Technology Assessment (NIHR HTA) Programme has commissioned this comparative research study in order to resolve this NHS decision problem.

The primary aim of UK COMPlex AneurySm Study (UK-COMPASS) is to answer the research question identified by the NIHR HTA Programme: ‘What is the clinical and cost-effectiveness of strategies for the management of juxtarenal AAA, including fenestrated endovascular repair?’ The five objectives of this study are shown in table 1.

**Table 1 T1:** The UK-COMPASS objectives

Objective 1	To compare different treatment strategies for their perioperative mortality and morbidity, corrected for confounding physiological and anatomical characteristics, in order to account for baseline risk and indication biases.
Objective 2	To identify whether particular physiological and/or anatomical baseline characteristics are associated with better clinical outcomes or better health economic efficiency using one or other treatment strategies.
Objective 3	To compare different treatment strategies in terms of overall survival and in terms of treatment failure in the long-term follow-up (stent-graft-related complications, secondary interventions, aneurysm-related mortality).
Objective 4	To perform cost-effectiveness analyses from NHS and personal social care perspective to establish incremental cost-effectiveness ratios, comparing different treatment strategies in terms of cost per incremental gain in and quality-adjusted life years.
Objective 5	To establish the clinical and cost utility of FEVAR and alternatives, in patients who are considered physiologically unfit for OSR, and to compare these against medical management.

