### Sample size calculations

#### Perioperative mortality

The primary outcome measure is perioperative death. The primary efficacy parameter is the OR comparing FEVAR with both open repair and off-label EVAR. For OSR, conservative estimate of 8% perioperative death might be expected, and a reduction to 4% could be considered clinically relevant, which is equivalent to an OR of 0.48 (based on NVR 2015 report^21^ and GLOBALSTAR registry^22^). This effect is slightly larger than that noted in randomised controlled trials of standard infrarenal aneurysm repair.^5^ A Bonferroni adjusted two-sided alpha level of 0.025 is used. Based on these assumptions, collecting data on 2000 patients will ensure a power in excess of 80% if the allocation between treatments is relatively equal and should be preserved above 70% even if one treatment strategy is used twice as much as the other two.

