#### Stratified comparative analysis for perioperative mortality and identification of risk factors

Based on the best available estimates, it is anticipated that 120 events (perioperative deaths) will be available if 2000 patients are included in the study. The aim is to identify anatomical/physiological characteristics for which there is a differential effect on patient outcome depending on the treatment strategy employed. We plan to use multivariable models which include propensity scores as continuous covariates, adjusted for appropriate confounding variables and including interaction effects with treatment effect. Using the statistical rule of thumb of 10 events per variable, approximately 12 variables can be included in any single model. If, for example, a two-level factor is to be investigated, main effects and interaction effects and a covariate of propensity scores will account for six variables, allowing for a further inclusion of other confounding variables as required.

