Models to estimate the propensity for each patient shall be generated using multivariable logistic modelling techniques using as candidate covariates only variables that influence simultaneously the treatment assignment and the outcome variable. Covariates shall be retracted to demographic/clinical data available at the point of treatment decision with the aim of producing a propensity model that satisfies the assumptions of conditional independence. The final analysis shall be carried out using stratified logistic where the strata are defined by the quintiles of the fitted propensity score values. Prior to analyses, it shall be confirmed that each stratum contains at least 20 observed perioperative deaths. If not, the strata will be combined with an adjacent strata level.

The key efficacy parameter of interest will be an OR presented with a 97.5% CI. Results will be presented as a forest plot with the OR within each stratum presented along with the overall effect.

Reports of HES data validation confirm high levels of completeness and accuracy. Therefore, missing data or inaccurate data are unlikely to be a significant problem. It is proposed that covariates with small amounts of missing data (≤10%) will be included on a complete case basis and covariates with a large amount of missing data (>10%) will be excluded from the analysis.

Sensitivity analyses are carried out to ensure the results are not sensitive to either the propensity model or the method of matching. With respect to the propensity model, sensitivity analyses shall be carried out by removing each covariate included in calculating the propensity score and repeating the analysis of the primary endpoints. The results of all sensitivity analyses shall be presented in a forest plot along with the overall effect from the primary analysis.

It is recognised that recruitment for site-reported QoL data will occur either side of a cessation of elective services in the UK due to the COVID-19 pandemic in 2020/2021. There may be differences in patient behaviour and clinical practice before and after this period and we aim to investigate this further in the analysis phase. First, outcome data before and after the dates of interest will be compared. Second, clinical practice before and after the dates of interest will be compared using data from the NVR.

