### Health economic analysis

The UK-COMPASS will adapt the recent National Institute for Health and Care Excellence (NICE) health economic analysis model^25^ which will facilitate updates of NICE Clinical Guideline ‘Abdominal Aortic Aneurysm–Diagnosis and Management (NG156)’.

Our aim is to inform NICE decision-making in a timely manner. The NICE health economic model has been developed from a UK NHS and Personal Social Services perspective, appraised by a NICE committee and scrutinised during consultation, and we see this fit to be adapted without developing a de novo model.

The purpose of the health economic analysis in this study is defined in the original objectives 4 and 5. The main outputs therefore will remain (a) estimation of incremental cost-effectiveness ratios comparing different treatment strategies in terms of life years and quality-adjusted life years gained, and (b) to identify whether particular level of physiological fitness (stratified into two groups) and/or anatomical baseline characteristics (stratified into three groups) are associated with better health economic efficiency using one or other treatment strategies.

At least 5-year follow-up is considered the essential minimum to capture attrition of treatment utility and accrual of treatment costs that occur from late failure/secondary intervention and postoperative surveillance.

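### For perioperative mortality the plan names only the odds ratio, and an odds-ratio interaction alone cannot show which fitness group avoids more deaths

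*Protocol article*

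**What the plan says.** The sample size section on perioperative mortality fixes the effect measure: "The primary efficacy parameter is the OR comparing FEVAR with both open repair and off-label EVAR". The Data analysis plan repeats it: "The key efficacy parameter of interest will be an OR presented with a 97.5% CI". The estimating model is described so: "The final analysis shall be carried out using stratified logistic where the strata are defined by the quintiles of the fitted propensity score values". The display follows the same scale: "Results will be presented as a forest plot with the OR within each stratum presented along with the overall effect". In that paragraph the strata are propensity quintiles, not fitness or anatomy groups.

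The target effect, by contrast, is justified by absolute risks: "conservative estimate of 8% perioperative death might be expected, and a reduction to 4% could be considered clinically relevant". The protocol equates this with an odds ratio of 0.48.

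For Objective 2, the section on stratified comparative analysis plans multivariable models with propensity scores as covariates, "adjusted for appropriate confounding variables and including interaction effects with treatment effect". It budgets about 12 variables against 120 expected deaths. The link function is not named.

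The Data analysis plan also divides patients by the British Aneurysm Repair Score into the highest-risk quartile and the remainder, and by neck length into three groups.

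Other outcomes have other scales: a log hazard ratio for long-term survival, and cost-effectiveness ratios in life years and quality-adjusted life years for the economic analysis, including by two fitness and three anatomy groups.

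**The concern.** The Introduction says that commissioners lack evidence "identifying which patients would benefit from this procedure", and Objective 2 asks which baseline characteristics go with better outcomes under which strategy. For an operation, the natural reading of benefit is deaths avoided per 100 patients, which is how the protocol itself argues clinical relevance.

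The only clinical route the protocol gives to that answer is an interaction term. For a binary outcome this is presumably on the log-odds scale. Absence of interaction on that scale means the same odds ratio in both groups, not the same number of deaths avoided. Presence of interaction does not by itself mean that the absolute gain differs. The gap between the two scales grows with the difference in baseline risk, and the risk-score split is designed to create such a difference. If only the odds ratio is reported, a reader could conclude that no group gains more when one gains several times more, or single out a group whose absolute gain is the same.

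**Working it through.** **Inputs from the protocol.** OSR mortality 8% and comparator 4% (sample size section); high-risk group = top quartile, so a 25%/75% split (Data analysis plan); 2000 patients in three groups, about 667 each if equal; 120 expected deaths.

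**Input not in the protocol.** The ratio R of baseline mortality, high-risk to standard-risk. It is assumed and varied.

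**1. The plan's own figure.** OR = (0.04/0.96)/(0.08/0.92) = 0.479. The stated 0.48 reproduces.

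**2. Constant odds ratio, different baseline risk.** With 8% overall, the standard-risk mortality is p = 0.08/(0.75 + 0.25R) and the high-risk mortality is Rp. Under odds ratio θ the treated risk is θp/(1 − p + θp), so the absolute reduction is p(1 − p)(1 − θ)/(1 − p + θp). At mortalities of this size it rises with p. For R = 3:

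- p = 0.08/1.5 = 5.33%; the high-risk group is at 16.0%.
- Standard risk: 5.33% falls to 2.63%, a reduction of 2.7 points (NNT 37).
- High risk: 16.0% falls to 8.36%, a reduction of 7.6 points (NNT 13).

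| R | Baseline, standard v high | Reduction in points, standard v high | Ratio of reductions | Interaction OR |
|---|---|---|---|---|
| 2 | 6.4% v 12.8% | 3.2 v 6.2 | 1.9 | 1 |
| 3 | 5.3% v 16.0% | 2.7 v 7.6 | 2.8 | 1 |
| 4 | 4.6% v 18.3% | 2.3 v 8.6 | 3.7 | 1 |

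Over R from 1.5 to 6 the ratio of reductions runs from 1.5 to 5.4.

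**3. The reverse: equal absolute reduction, R = 3.**

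- 4 points in each group: 5.33% to 1.33% gives OR 0.24; 16% to 12% gives OR 0.72; ratio of odds ratios 3.0.
- 2 points in each group: 5.33% to 3.33% gives OR 0.61; 16% to 14% gives OR 0.86 (0.855); ratio of odds ratios 1.4.

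Chance that such an interaction reaches two-sided 5% significance (Wald test, 667 per strategy, no covariates): the standard error of the log ratio of odds ratios is the square root of the sum of 1/(np) + 1/(n(1 − p)) over the four cells. For 4 points it is 0.541, so z = ln(2.98)/0.541 = 2.02 and the chance is about 52%. For 2 points it is 0.443, z = 0.75, and the chance is about 11%.

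**4. How precise the absolute contrast would be.** At R = 3 with a constant odds ratio, the two risk differences differ by 4.9 points. The standard error of that contrast is the square root of the sum of p(1 − p)/n over the four cells, 3.8 points. A 95% interval is therefore about ±7.4 points (1.96 × 3.77), and the chance of significance is about 26%.

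**5. Limit on subgrouping.** Three strategies × three neck groups × two risk groups = 18 cells; 120/18 = 6.7 deaths per cell on average.

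**The case against.** The strongest reply is that nothing stated is wrong. The odds ratio is named consistently, 0.48 is right, and naming it as the key parameter does not exclude absolute risks, which the unseen statistical analysis plan may add. The logistic link for the interaction models is inferred, and no sentence says that a null interaction will be read as equal benefit. All of this stands. It makes the point a recommendation about an incomplete choice of scale, not a correction of an error. It does not remove it, because the protocol names one scale for its main outcome and gives none for judging heterogeneity, while stratifying on a variable that makes the scale matter.

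Three stronger readings are tempting, and the documents do not support them.

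- A reader might infer that the odds ratio is the only efficacy scale in the study. Survival uses the hazard ratio, and the economic section looks at whether fitness and anatomy groups "are associated with better health economic efficiency using one or other treatment strategies", on a life-year and QALY scale.
- A reader might infer that the economic model is left without absolute mortality risks. The protocol adapts an existing NICE model whose inputs are not shown, and absolute risks can be obtained by applying an odds ratio to a baseline risk, as done above.
- A reader might infer that the difference between a stratum-conditional and a marginal odds ratio distorts the result. In the R = 3 example, treated mortality is 0.75 × 2.63% + 0.25 × 8.36% = 4.06%, a marginal odds ratio of 0.487 against 0.479. That is negligible.

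It is also fair to object that subgroup risk differences will be imprecise. Steps 4 and 5 confirm it, and the change below is limited accordingly.

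**Conclusion.** The point holds for perioperative mortality and Objective 2. The odds ratio is the only effect measure named for that outcome, and with fitness groups defined by predicted risk it cannot alone show which group avoids more deaths. Under a constant odds ratio of 0.48 the absolute benefit differs about 1.9-, 2.8- or 3.7-fold for an assumed baseline risk ratio of 2, 3 or 4. The opposite error, an apparent interaction where absolute benefit is equal, depends heavily on effect size: at a ratio of 3 it is marked for an equal 4-point benefit and slight for an equal 2-point benefit.

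These sizes rest on an assumed mortality ratio between fitness groups, on 8% OSR mortality applying to the whole 25%/75% population, and on reading the interaction models as logistic. The direction of the argument needs only that baseline mortality differs between the groups and that the effect is not null. The change is worth making because it costs little. It does not affect the validity of the primary test.

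**What to change.** Keep the odds ratio with its 97.5% CI as the primary test, with alpha unchanged, and add the following.

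1. State the link function of the Objective 2 models, and so the scale on which interaction is assessed.
2. From the planned models, report standardised perioperative mortality for each strategy and the risk differences FEVAR v OSR and FEVAR v EVAR, with delta-method or bootstrap CIs (97.5% overall, to match the odds ratio). If the stratified logistic analysis is fitted conditionally it yields no absolute risks. In that case enter the propensity quintile as a model factor, or average the within-quintile risks over a common population.
3. Give the same quantities by risk group and, separately, by neck-length group. Do not cross the two, given about 120 deaths.
4. Interpret Objective 2 on both scales, and say so when they disagree.

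Cost: a little more analysis and some extra table columns; no new data. The subgroup intervals will be wide, so they should be labelled exploratory, and an interval that spans zero should not be read as equal benefit.

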#### Routinely collected data

This stream pertains to patients who have undergone repair of a complex aneurysm in England, over a 2-year period between 1 November 2017 and 31 October 2019. Duration of inclusion period was estimated to be 2 years commencing as soon as regulatory approvals are in place, anticipating at least 30% of aneurysms to fulfil inclusion criteria in order to provide adequate statistical precision. Health data, demographic data and healthcare resource use data relating to operated patients will be retrieved from Hospital Episode Statistics (HES) datasets (NHS Digital), the National Vascular Registry (NVR), and the NHS Picture Archiving and Communication System (PACS). Median follow-up will be 5 years, until 31 October 2023.

The NVR is run by the Clinical Effectiveness Unit of the Royal College of Surgeons of England as a national clinical audit. Audit of NVR data revealed 95% case ascertainment and data completeness between 85.5% and 100% depending on the data point, with a median completeness of 93.3%. Data capture system incorporates a number of validations ensuring high level of accuracy.^1^ The NVR includes a wide range of data relevant to this study, including demographics, comorbidity, preoperative assessment, intraoperative detail, postoperative complications, duration of hospital stay and critical care use for all types of AAA repair.

HES is a data warehouse containing details of all admissions, outpatient appointments, investigations and emergency department attendances at NHS hospitals in England. These data are collected during a patient’s time at hospital and are designed to enable administration as well as medical research. In addition to health and resource use data during the primary admission for aneurysm repair, follow-up data will be collected for 5 years after the operation to identify late complications, treatment of complications and re-interventions. Survival data are retrieved via Office for National Statistics data linked to HES. The quality of HES data is recognised to be adequate for research and is regularly used for research purposes.^18^

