### Data analysis plan

Analyses will be carried out on an intention-to-treat basis, retaining all patients in the surgery group to which they are assigned irrespective of any procedural issues. The intervention groups will be OSR, FEVAR, EVAR±adjuncts (including chimneys and endoanchors). The exact treatment received will be determined by triangulation of NVR data and HES data for OSR. Patients receiving endovascular treatment will be identified from NVR data and HES data, and exact technical details of each procedure (including the use of adjuncts) will be determined through analysis of procedural images in the Corelab.

As an analysis of observational cohort data, all attempts to present a measure of efficacy free from confounding bias will be undertaken. Patients will be stratified by infrarenal neck length for analysis into three groups: 0-4 mm (juxtarenal), 5–9 mm (juxtarenal) and ≥10 mm neck length (not juxtarenal but complex based on device-specific IFU criteria). This will serve to limit anatomical heterogeneity and bias within comparisons. Additionally, patients will be stratified by physiological risk. The British Aneurysm Repair Score^23^ will be used (11 clinical parameters available from NVR data) to divide each comparison group into those that are high risk (the highest risk quartile) and the remainder as standard risk.

Statistical analyses of the primary outcome shall follow the principle of propensity score analysis. Propensity score estimation is chosen for the analysis of the primary endpoint instead of multivariable regression techniques because it is considered the most appropriate means of accounting for selection bias at the low level of perioperative death rates anticipated.^24^ Propensity scores estimate the probability of a patient being given each treatment strategy based on baseline clinical and demographic characteristics. Patients can then be stratified based on their propensity to receive each treatment strategy and an estimate of treatment effect is then obtained, which adjusts for potential selection bias in the data.

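### The missing-data rule rests on HES completeness although the risk-score items come from the NVR, does not cap the joint complete-case loss, and could remove a confounder for missingness alone

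*Protocol article*

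**What the plan says.** The Data analysis plan fixes a two-part rule for covariates. At or below the limit, "covariates with small amounts of missing data (≤10%) will be included on a complete case basis". Above it, "covariates with a large amount of missing data (>10%) will be excluded from the analysis". The reason given is that "Reports of HES data validation confirm high levels of completeness and accuracy", from which the article concludes that missing data should not matter much.

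The same section splits each comparison group by the British Aneurysm Repair Score, described as "11 clinical parameters available from NVR data". The account of the NVR under Overview, Routinely collected data, reports "data completeness between 85.5% and 100% depending on the data point, with a median completeness of 93.3" per cent.

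Candidates for the propensity model are limited to variables known at the treatment decision that influence both treatment and outcome. The stated aim is conditional independence.

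**The concern.** The source cited for completeness is not the source of the physiological risk parameters. The NVR range means that at least one NVR data point is 14.5% missing, above the limit, and that half of them are 6.7% or more missing.

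Two things follow.

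- A patient with any one included covariate missing drops out of a complete-case analysis. A limit of 10% on each covariate therefore places no limit of 10% on the whole.
- The exclusion above 10% looks only at missingness. By the protocol's own definition every propensity candidate is a confounder, so any candidate it removes leaves its confounding in the odds ratio.

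This is a non-randomised comparison whose credibility rests on adjustment for fitness and anatomy. Residual confounding, selection of patients with complete records and loss of power are all at stake.

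**Working it through.** **Inputs.**

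- NVR completeness: 85.5% to 100%, median 93.3% (Overview, Routinely collected data).
- Risk parameters: 11 (Data analysis plan). For scale, the section on stratified comparative analysis says "approximately 12 variables can be included in any single model", but that refers to the interaction models. The size of the propensity model is not stated.
- Effect: "conservative estimate of 8% perioperative death might be expected, and a reduction to 4% could be considered clinically relevant". Error rate: "A Bonferroni adjusted two-sided alpha level of 0.025 is used". 2000 patients in three groups, power above 80% if roughly equal (Sample size calculations, Perioperative mortality).
- Deaths: 120 in 2000, that is 6%.
- Expected eligible patients: about 3000 (Methods, Routinely collected data).

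**The plan's own power.** With n per group, power = Φ[(0.04√n − 2.2414√(2 × 0.06 × 0.94)) / √(0.08 × 0.92 + 0.04 × 0.96)]. At n = 2000/3 ≈ 667 this is Φ[(1.0331 − 0.7528)/0.3347] = Φ(0.837) = 79.9%. For 80%, 669 per group are needed. The plan's figure is reproduced to within rounding.

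**Joint loss, assuming k = 11 covariates each c = 0.933 complete.**

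- Missingness falls in the same patients: loss = 1 − c = 6.7%.
- Missingness is independent: loss = 1 − 0.933^11 = 1 − 0.466 = 53.4%.
- Missingness never overlaps: loss = 11 × 0.067 = 73.7%.
- In between, with equal correlation on a Gaussian copula: 44% at 0.2, 32% at 0.5, 20% at 0.8.
- Fewer covariates, independent: 1 − 0.933^5 = 29%; 1 − 0.933^8 = 43%.

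**Both halves of the rule together.** Assume that each covariate's completeness lies with probability one half uniformly in 85.5% to 93.3%, and otherwise uniformly in 93.3% to 100%, with independent missingness.

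- Chance of falling below 90% and being dropped: 0.5 × 4.5/7.8 = 0.288. Expected number dropped: 11 × 0.288 = 3.2.
- Mean factor retained per covariate: 0.288 × 1 + 0.212 × 0.9165 + 0.5 × 0.9665 = 0.966. To the power 11 this is 0.68, so about 32% of patients are lost. In simulation, 95% of draws lost 16% to 46%.

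**Power at equal allocation, same formula.**

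| Loss | From 2000 | From 3000 |
|---|---|---|
| 6.7% | 76.8% | 92% |
| 30% | 63% | 82% |
| 53.4% | 44% | 63% |

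**Propensity strata.** The plan wants at least 20 deaths in each quintile. With no loss, 120/5 = 24 on average. At 53.4% loss from 2000, about 56 deaths remain, so at most two strata can hold 20. From 3000 about 84 remain, so at most four can.

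**The risk score.** It needs all its items. Two items each 6.7% missing independently already leave 1 − 0.933² = 13% of scores incomplete, above the plan's own limit.

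**The case against.** A reader might infer that the protocol's own figures imply the loss of about half the patients and the deletion of known confounders. The documents do not support that, for these reasons:

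- The one-half figure needs 11 covariates at the overall NVR median and independent missingness. The article states neither. Nor is one half an upper limit.
- The two harms partly offset. In the 53% scenario every covariate stays under 10% missing, so none is dropped. Where covariates are dropped, fewer patients are lost.
- The completeness range covers NVR data points in general, including intraoperative and postoperative fields. The item at 85.5% is not identified. It may be one that could not enter the propensity model anyway.
- Covariates also come from HES and from Corelab CT. The 11 parameters are named for risk stratification, and the article does not say that all of them enter the propensity model.
- About 3000 eligible patients are expected. At 32% loss, 2040 remain, or 680 per group, more than the 669 needed for 80% power.

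All of this stands. It limits the size of the problem but does not rescue the rule. A larger cohort restores precision; it does not remove confounding from an omitted covariate or any selection of patients with complete records. The planned sensitivity analysis removes included covariates one at a time, so it shows nothing about those already excluded or about the incomplete records. Nor is this detail left to an unseen analysis plan: the article states the rule itself.

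**Conclusion.** The concern holds in conditional form. The rule is justified by the wrong source, does not bound the joint loss, and decides on confounders by missingness rather than by importance.

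The size is uncertain: about 7% to 74% of patients lost for 11 covariates at 93.3%, and about one third, with about 3 of 11 covariates dropped, under the assumed spread with independence. Whether planned power survives depends on whether the cohort is nearer 2000 or 3000.

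Removal of a confounder remains a risk, because the article does not show that any baseline item exceeds 10% missing. Whether complete-case selection biases the odds ratio depends on why data are missing, which the article does not describe.

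**What to change.** Replace the two-part rule with multiple imputation. The imputation model should include treatment, outcome, all propensity and risk-score items, and auxiliary variables from HES. Estimate the propensity score within each imputed set, run the stratified analysis in each, and pool by Rubin's rules.

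Do not exclude a covariate on missingness alone. Base the completeness statement on the NVR as well as HES, and report the joint completeness of the chosen covariates and of the risk score. Keep the complete-case analysis as a sensitivity analysis.

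The cost is a change of wording and modest analyst time, with no new data. The price is reliance on a missing-at-random assumption, which should be stated.
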